##### Aerobic ET

The aerobic component of the program will consist of both continuous steady state and interval-based training to provide varied forms physiological perturbation to the different components of the oxygen cascade that could be affected by chemotherapy [46]. Interval sessions will be performed on a cycle ergometer, whilst the continuous training will be performed on an upright cycle, treadmill and/or elliptical trainer based on participant preference. Exercise intensity will be individualised from each participant’s percentage of heart rate reserve (%HRR) at their ventilatory threshold (VT) measured during the baseline cardiopulmonary exercise test (CPET). Aerobic exercise intensity will be monitored by the 1–10 rating of perceived exertion (RPE) scale and wrist-worn heart rate (HR) monitors (Polar M200, Polar, Kempele, Finland), and these will be used to adjust the exercise workloads to account for day-to-day variation in participant health status throughout each chemotherapy cycle. The program will be broken into four training blocks based on participant’s scheduled chemotherapy in weeks 0, 3, 6 and 9 with progression of training volume outlined in Table 1. All sessions will include a 5-min aerobic warm up and cool-down. Following a one-week lead in period consisting of 3 sessions of 30-min at an intensity 10–15 beats/min below the VT, participants will complete two steady state aerobic sessions and one vigorous to high intensity interval session per week for the remaining 11 weeks, with progressive increases in exercise duration and/or intensity as outlined in Table 1. Interval sessions will begin in week 2, and consist of four work intervals of 2–4 min progressing from the %HRR corresponding to VT and progressing to 85–95% HR_peak_, interspersed with 3-min of cycling at a light intensity. The target intensity of the continuous and interval training will be reduced by ~ 5% in week 3, 6 and 9 to account for the increased symptom burden of each chemotherapy cycle.

**Table 1 Tab1:** Progression of the 12-month multi-modal exercise training program

Phase	Cycle	Weeks	Session Type	Frequency (per week)	Duration/Dose	Intensity^**a**^
Phase 1 Supervised Exercise During AC	1	1–3	Steady State & Resistance Training	2	SS: 30 mins RT: 1–2 sets × 12–15 reps	SS: 10–20 b/min below %HRR at VT RT: 60–70% 1RM
			Interval Training	1	4 × 2 mins^b^	%HRR at VT ± 5 b/min

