### Usual care group

Participants allocated to usual care will receive ongoing care from their oncology team but will not receive additional access to supervised exercise training from the research team. Control group participants will receive usual lifestyle advice as part of their routine clinical care in which patients will be provided a copy of the Cancer Council Australia booklet entitled “Exercise for People Living with Cancer.” Exercise will then be left to the patient’s volition, including any decision to enrol in a structured exercise program. A sham exercise comparator group will not be used because our primary outcome is an objective, measurable endpoint that is not subjected to patient expectancy or placebo effects.

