### ET adherence and attendance

Attendance and adherence to the prescribed number of exercise sessions, and dose within each exercise session (both supervised and unsupervised) throughout the 12-month intervention will be assessed using the Physitrack online patient software which will be logged by participants during each session. Attendance will be calculated from the number of sessions completed versus number prescribed per week. Adherence to the aerobic training will be calculated from the prescribed vs completed duration and intensity of aerobic exercise, whilst adherence to the resistance training will be assessed from the prescribed vs completed repetitions and weight. For the supervised sessions during Phase 1 and 2, trainers will record reasons for modification (increase or decrease) to the prescribed dose of aerobic and/or resistance exercise during each session.

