### Sample size calculation and statistical analysis

Our sample size of 100 subjects will address Aims 1 and 2 with sufficient compensation for expected attrition of 10% based on our previous pilot work in which two women withdrew (moved interstate and severe treatment related illness) [32]. Primary and secondary analyses will be analysed on an intention-to-treat basis in line with the CONSORT guidelines. Participants who discontinue the intervention will still be asked to attend follow-up evaluations and their results will be included within the intention-to-treat analysis. The significance level for statistical analysis will be set at 5%.

The sample size estimations for Aim 1, that significantly fewer patients undergoing exercise therapy will be functionally disabled at 12 months, are based on our pilot study in which 29% of the total cohort met this criteria at treatment completion and in which there was a 7-fold greater proportion of functional disability in the usual care arm (Usual care: 50% vs Exercise Training: 7%) [32]. In the current proposal, we have used a conservative 24% incidence of functional disability (cf. 29% in the pilot) and three-fold difference between groups (cf. 7-fold in the pilot) [32]. To detect a 36% vs 12% difference in the prevalence of functional disability, 45 women in each group is required (β = 20%, α = 5%). Generalised linear mixed models (GLMMs) with participants as the random effect, time as a repeated measures, and group and group-by-time interactions as the fixed effects, will be used to evaluate the differential effects of the intervention on the incidence of functional disability and additional secondary outcomes. All data will be analysed unadjusted, and adjusted for models including potentially important covariates found to be significantly different between groups at baseline that could explain residual outcome variance. No imputation will be performed for subjects who have missing data due to dropping out of the study. Pre-planned per-protocol analysis including only subjects attending > 66% of the planned exercise sessions will explore the influence of exercise adherence on the primary and secondary outcomes.

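### The exploratory per-protocol rule cannot be applied to usual-care women, and keeping all controls would compare exercisers selected after randomisation with an unselected arm

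*Protocol article*

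**What the plan says.** In the Protocol article, the section on sample size and statistical analysis makes intention to treat the basis of inference: "Primary and secondary analyses will be analysed on an intention-to-treat basis in line with the CONSORT guidelines". The same paragraph ends with a "Pre-planned per-protocol analysis including only subjects attending > 66% of the planned exercise sessions", which "will explore the influence of exercise adherence on the primary and secondary outcomes". The section on ET adherence and attendance gives the measure behind the threshold: "Attendance will be calculated from the number of sessions completed versus number prescribed per week". The section on the usual care group says that these women "will not receive additional access to supervised exercise training from the research team", and adds: "Exercise will then be left to the patient’s volition, including any decision to enrol in a structured exercise program".

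The article names no comparator for the per-protocol set and gives no rule for controls. The only covariate adjustment it describes is for characteristics that differ significantly between the randomised groups at baseline.

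**The concern.** An attendance threshold needs a denominator of prescribed sessions, and only the exercise arm has one. A rule that admits only women above the threshold therefore admits no control, and no between-arm contrast is left.

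The obvious workaround keeps every control and only the adherent exercisers. That selects one arm on something observed after randomisation and leaves the other arm unselected. The article itself gives reasons to expect attendance to track health during chemotherapy. Training intensity is lowered "to account for the increased symptom burden of each chemotherapy cycle", and in the pilot "two women withdrew (moved interstate and severe treatment related illness"), so one of the two pilot losses was due to illness. Women who tolerate treatment poorly may both miss sessions and have a lower VO2peak at 12 months. Dropping them from one arm only would lower the apparent prevalence of disability there, whatever exercise does.

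What is at stake is the reading of a secondary result. The analysis covers the primary outcome and all secondary outcomes, and a reader could take it as the effect of exercise in women who actually did it.

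**Working it through.** **Yardstick from the plan.** The design contrast is 36% versus 12% disabled, a difference of 24 percentage points, with an overall incidence of 24%. With two-sided 5% and 80% power (sidedness is not stated), the unpooled formula gives (1.960 + 0.842)² × (0.36×0.64 + 0.12×0.88) / 0.24² = 45.8 per arm, close to the stated 45. Then 45/0.9 = 50 per arm, or 100 in total. The sample size does not depend on this point.

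**Literal reading.** The exercise programme prescribes 12×3 + 14×4 + 26×4 = 196 sessions (phase descriptions and Table 1). Exceeding 66% means more than 129.4, so at least 130 sessions. Usual care has 0 prescribed sessions, so attendance is undefined and no control qualifies.

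**All controls kept: null model.** Assume exercise has no effect and 24% are disabled in both arms. Let 12-month fitness and attendance propensity be bivariate normal with correlation r, and let a fraction f of the exercise arm exceed the threshold. Neither f nor r is in the article; both are assumptions.

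Prevalence among adherers = P(fitness < Φ⁻¹(0.24) and attendance > Φ⁻¹(1−f)) / f.

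Example with f = 0.6, r = 0.5: the cut-offs are −0.706 and −0.253, the joint probability is 0.080, and 0.080/0.6 = 0.133. The spurious reduction is 0.240 − 0.133 = 0.107.

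| f | r | Adherers disabled | Spurious reduction (points) |
|---|---|---|---|
| 0.6 or 0.7 | 0 | 24.0% | 0 |
| 0.7 | 0.2 | 20.8% | 3.2 |
| 0.7 | 0.5 | 15.3% | 8.7 |
| 0.6 | 0.2 | 19.9% | 4.1 |
| 0.6 | 0.5 | 13.3% | 10.7 |

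The range is about 3 to 11 points. At f = 0.8 it is 2.3 to 6.4 points. With a 36% risk in both arms and f = 0.6-0.7 it is 3.8 to 12.8 points.

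**Chance of a false significant result.** Use a pooled z-test against 45 controls. At f = 0.6, r = 0.5 there are 27 adherers. The pooled proportion is (45×0.24 + 27×0.133)/72 = 0.200, the null standard error 0.0974 and the actual standard error 0.0912. This gives Φ((0.107 − 1.96×0.0974)/0.0912) ≈ 18%. At f = 0.7, r = 0.2 it is about 5%. The nominal rate in favour of exercise is 2.5%.

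**Second model.** Take a risk of 36% in both arms, 60-80% adherent, and non-adherers at 1.5 to 3 times the odds of disability of adherers. The spurious reduction is 1.9 to 10.1 points and the false-positive rate for exercise 3.7% to 13.5%. At an odds ratio of 1 they are 0 and 2.5%.

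**Role of baseline.** Let attendance relate to 12-month fitness only through baseline fitness (assumed baseline to 12-month correlation 0.6-0.8). The crude gaps stay at about 3 to 11 points, but the gap conditional on baseline is zero within simulation error. At correlation 0.8, f = 0.6 and r = 0.5, adherers' prevalence is about 10% at baseline and 13% at 12 months, so a contrast of change over time would not favour exercise. Adjustment for baseline therefore removes the part of the bias that baseline fitness carries. It does not remove a part that arises from illness during treatment.

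**The case against.** The strongest reply is that the article never says adherers will be compared with all controls. A within-arm comparison of adherers and non-adherers also fits its wording, and in an exercise trial an attendance threshold is usually understood to apply to those who were prescribed exercise. That is fair, and the comparison with all controls is an inference. It does not clear the text: the stated rule admits only women above the threshold, and a within-arm comparison is observational too, with no adjustment planned for how adherers differ from non-adherers.

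Second, intention to treat governs, women who stop the intervention are still followed up, and the per-protocol analysis is described as exploring adherence. This stands in full. A reader might infer that the analysis could be used to rescue a negative trial; nothing in the article supports that.

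Third, a reader might infer that the comparison is bound to show a benefit when exercise does nothing. The documents do not support that either. The bias needs attendance to be prognostic, the article gives neither an adherence rate nor such a correlation, and a significant false benefit stays improbable across the assumed ranges. The crude figures also leave out the baseline measurement, which the planned repeated-measures mixed model includes.

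Fourth, a complier-average effect has its own bias. With randomisation as the instrument it assumes that assignment does nothing below the cut-off, yet a woman attending 129 of 196 sessions has exercised a good deal. If women below the cut-off gain a fraction k of the benefit, the estimate is inflated by the factor 1 + k(1−f)/f: 1.11 at f = 0.7, k = 0.25, and 1.33 at f = 0.6, k = 0.5. This stands, and it is why that estimate belongs beside the other analyses and not in their place.

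**Conclusion.** The point holds in limited form. The per-protocol population is defined by a quantity that one arm does not have. The literal reading leaves no comparison, and keeping all controls gives one that randomisation does not protect. The likely direction favours exercise, because the article ties both exercise tolerance and withdrawal to treatment symptoms or illness. The size is conditional: about 3 to 11 crude percentage points against a planned 24, under assumed adherence of 60-70% and correlation of 0.2-0.5. It is zero if attendance is not prognostic, and less to the extent that baseline VO2peak accounts for the link. The primary conclusion, the sample size and the type I error of the intention-to-treat analysis are untouched. The wording should be corrected before the analysis is run, but it does not threaten the trial's main result.

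**What to change.** 1. State that the attendance rule applies to the exercise arm only and that all usual-care women are kept in this comparison.
2. Adjust the comparison for baseline VO2peak and the stratification factors (age group and HER2 status). Report it as descriptive and non-causal, without a confirmatory p-value.
3. Add a supplementary complier-average causal effect of exceeding 66% attendance, with randomisation as the instrument and all randomised women kept in their arms. Show its sensitivity to a lower cut-off or to attendance as a continuous dose.

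The cost is a few sentences in the analysis plan and one further analysis. Attendance is already logged, and women who discontinue are already asked back for assessment. The downside is a wider confidence interval, and the assumption that assignment has no effect below the cut-off. If that assumption is false the estimate is inflated, by roughly 10-35% under the values shown above, so the caveat should be reported with the result.

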To compare the current standard-of-care (resting LVEF) to measures of cardiac reserve (peak exercise cardiac output; Qc) as predictors of functional disabilityTo determine whether a 12-month structured exercise training (ET) program reduces the proportion of BCa patients who are functionally disabled 12-months after the initiation of AC.

We hypothesize that:
Cardiac reserve will be superior to resting LVEF at predicting the development of functional disability 12-months following ACParticipating in a 12-month structured ET will reduce the proportion of patients who are functionally disabled 12-months following AC.

Secondary aims include assessing the effect of ET on changes in cardiopulmonary fitness and cardiac reserve, along with indices of resting cardiac structure and function, vascular stiffness, biochemical and blood-based markers of cardiovascular function, total- and regional body composition, bone mineral density of the lumbar spine and femoral neck, muscle strength, physical function, habitual physical activity, cognitive function, and multidimensional quality of life.

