### Primary and secondary outcome measures

The primary outcome for this study will be the prevalence of functional disability (defined as VO_2_peak ≤ 18.0 mL/kg/min) measured via CPET at 12 months. The predictive ability of standard-of-care versus novel cardiac reserve measures will be addressed by comparing LVEF assessed via 3-dimensional (3D) echocardiography to cardiac reserve assessed via exCMR. For the purposes of this study, impaired cardiac reserve will be defined as a < two-fold increase in Qc from rest to peak exercise [33]. Impaired LVEF will be defined as a LVEF < 53% which is in line with current cardio-oncology guidelines [14, 15, 17].

Secondary outcomes will include changes in cardiopulmonary fitness and cardiac reserve, along with indices of resting cardiac structure and function, vascular stiffness, biochemical and blood-based markers of cardiovascular function, total- and regional body composition, bone mineral density of the lumbar spine and femoral neck, muscle strength, physical function, habitual physical activity, cognitive function, and multidimensional quality of life.

Additional exploratory outcomes will include the association between changes in cardiopulmonary fitness with indices of cardiac (cardiac reserve) versus non-cardiac factors (central vascular stiffness, haemoglobin concentration, lower body lean body mass, skeletal muscle composition of the thigh). The study will also explore the effect of the intervention on treatment-related variables including the dose of treatment received and response to neoadjuvant therapy.

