The second primary aim of the study is to compare the predictive ability of standard-of-care measures (LVEF) with peak Qc measured by ExCMR in identifying women who will meet criteria for functional disability at 12 months. A multivariate regression will be used with five variables entered (age, LVEF, GLS, study group and peak Qc). The analysis will be stratified for group allocation (usual care vs exercise training) to account for the potential influence of the exercise intervention on the incidence of functional disability at 12-months. The sample size estimated for such an analysis can be calculated as 90 women (50 + 8 x no. of variables) using the method suggested by Green [74].

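### The prediction aim hypothesises that cardiac reserve beats resting LVEF, but the regression fixed for it contains no test of one marker against the other

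*Protocol article*

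**What the plan says.** All references are to the protocol article; no separate analysis plan is at hand.

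- Background, hypotheses: "Cardiac reserve will be superior to resting LVEF at predicting the development of functional disability" at 12 months.
- Sample size calculation and statistical analysis: the second primary aim is stated as follows: "compare the predictive ability of standard-of-care measures (LVEF) with peak Qc measured by ExCMR in identifying women who will meet criteria for functional disability"; the time point given is the 12-month visit. (Background lists this aim first; the abstract and the statistics section list it second.)
- Same section, the model: "A multivariate regression will be used with five variables entered (age, LVEF, GLS, study group and peak Qc").
- Same section, next sentence: "The analysis will be stratified for group allocation (usual care vs exercise training").
- Same section, the size: "The sample size estimated for such an analysis can be calculated as 90 women (50 + 8 x no. of variables").
- Primary and secondary outcome measures: the outcome is binary, the "prevalence of functional disability (defined as VO_2_peak ≤ 18.0 mL/kg/min) measured via CPET at 12 months". This section says that LVEF and cardiac reserve will be compared, but supplies only cut-offs: "impaired cardiac reserve will be defined as a < two-fold increase in Qc from rest to peak exercise", and LVEF below 53%.
- Cardiac reserve section: reserve is the change in Qc from rest to the high-intensity workload. The regression names peak Qc.

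**The concern.** A hypothesis that one predictor is better than another needs a statistic that sets the two against each other. A regression holding both returns two coefficients, each with a test against zero. A small p-value for one and a large p-value for the other is not evidence that they differ. Their raw coefficients cannot be compared either, because Qc and LVEF are in different units.

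Two further features matter. GLS and LVEF both come from the resting echocardiogram. If they are correlated, LVEF's coefficient is estimated less precisely while Qc's is not penalised in the same way, which tilts significance toward Qc, the marker that the hypothesis favours. And study group is entered as a predictor while the analysis is also stratified by it, so it is unclear whether the answer comes from one pooled model or from two within-arm models.

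At stake is one of the trial's two primary conclusions: whether exercise CMR predicts disability better than the standard of care.

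**Working it through.** **1. The plan's own figure.** 50 + 8 × 5 = 90, and 90 / (1 − 0.10) = 100. Both reproduce. The 90 follows from a count of variables; no difference between the markers enters it.

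**2. Events available.** The article says "we have used a conservative 24% incidence of functional disability", split 36% and 12% by arm; (36% + 12%) / 2 = 24%.
- Pooled: 0.24 × 90 = 21.6 events, 21.6 / 5 = 4.3 per variable.
- Usual care: 0.36 × 45 = 16.2. Exercise: 0.12 × 45 = 5.4.
- Within an arm study group is constant and drops out. The four remaining variables have 16.2 / 4 = 4.1 and 5.4 / 4 = 1.4 events each.

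**3. How often equal markers look unequal.** Inputs from the article: n = 90, 45 per arm, 36% and 12%, five variables, 5% significance level (taken as two-sided). Assumed, because the article gives none: standardised normal markers, the same true odds ratio (OR) per SD for Qc and LVEF, GLS with no effect of its own and correlated with Qc as LVEF is, pooled logistic model, Wald tests. There were 3,000 trials per setting; non-converging fits (at most 0.5%) were dropped. The contrast is z = (b_Qc − b_LVEF) / √(V_Qc + V_LVEF − 2·Cov).

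All rows have Qc–LVEF correlation 0.3:

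| OR per SD, both markers | LVEF–GLS correlation | Qc only significant | LVEF only | Exactly one | Contrast rejects, either direction |
|---|---|---|---|---|---|
| 1 (no effect) | 0.5 | 4.9% | 4.7% | 9.6% | 4.6% |
| 1.5 | 0.5 | 23.4% | 17.5% | 40.9% | 5.1% |
| 2 | 0 | 26.1% | 29.8% | 55.9% | 5.7% |
| 2 | 0.5 | 28.4% | 24.4% | 52.8% | 4.6% |
| 2 | 0.7 | 38.8% | 17.5% | 56.3% | 5.2% |
| 3 | 0 | 11.9% | 15.5% | 27.4% | 5.0% |
| 3 | 0.5 | 18.7% | 12.0% | 30.7% | 5.3% |
| 4 | 0.5 | 9.0% | 5.4% | 14.4% | 4.3% |

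Over all settings with OR 1.5 to 3 and Qc–LVEF correlation 0 to 0.5, Qc alone was significant in 12% to 39% and exactly one marker in 21% to 59%. The contrast rejected in 4.0% to 5.7% in every setting (simulation error near 5%: √(0.05 × 0.95 / 3000) = 0.4 points). Two further simulations at 0.4 to 1.0 log-odds per SD (OR 1.5 to 2.7), under other assumed correlations, gave Qc alone in 12% to 30% (GLS as uncorrelated noise) and in 22% to 42%. In the latter, the contrast favoured Qc in 1.9% to 3.3%, against a one-sided nominal 2.5%. The combined range is 12% to 42%.

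**4. Analytic check.** For two independent tests with equal power p, P(exactly one significant) = 2p(1 − p), at most 2 × 0.5 × 0.5 = 50%. With unequal power, P(Qc only) is about p_Qc(1 − p_LVEF). In the row with OR 2 and LVEF–GLS correlation 0.7, both were significant in 20.4%, so p_Qc = 38.8% + 20.4% = 59.2% and p_LVEF = 17.5% + 20.4% = 37.9%. Then 0.592 × (1 − 0.379) = 36.8%, close to the simulated 38.8%.

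**5. Why GLS tilts it.** Ignoring the other covariates, a correlation r with GLS multiplies the variance of LVEF's coefficient by about 1 / (1 − r²): 1.33 at r = 0.5 and 1.96 at r = 0.7.

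**6. Power of a direct test at n = 90** (assumed Qc–LVEF correlation 0.3, LVEF–GLS 0.5; Qc effect against LVEF effect in log-odds per SD). The coefficient contrast is taken from the stated five-variable model; the AUC difference is between models sharing age and group.

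| True effects | Coefficient contrast | Paired AUC difference |
|---|---|---|
| 0.7 vs 0 (OR 2 vs 1) | 28% | 12% |
| 1.1 vs 0 (OR 3 vs 1) | 54% to 56% | 39% to 41% |
| 1.1 vs 0.4 (OR 3 vs 1.5) | 25% to 26% | 22% |

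With equal markers the AUC test favoured Qc in 0.6% to 2.7%, so it is conservative when effects are weak.

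**The case against.** The best defence is that this is a journal article, and the comparison made after fitting is a detail that an analysis plan may supply. The model is not incompatible with the hypothesis: a contrast of standardised Qc and LVEF coefficients can be drawn straight from it. That stands, and it is why the fix is short. It does not dispose of the point. The article does not defer this analysis; it fixes the model, the five variables, the stratification and the sample size, and none of these contains a comparison of the two markers.

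Some stronger readings are tempting, and the text does not support them:

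- A reader might infer that the plan commits to declaring superiority when Qc is significant and LVEF is not. It states no rule. The 12% to 42% is the price of one natural reading.
- A reader might infer that the aim itself asserts superiority of peak Qc. The aim is to compare; superiority is in the hypothesis and concerns cardiac reserve.
- Because the regression names no visit, a reader might suppose that the 12-month scan could be the predictor. The aim speaks of women who will go on to meet the criteria, which leaves only baseline or 4 months open.
- Stratified may mean one model with arm-specific baselines and not two separate fits. Study group as a covariate would then be redundant rather than inestimable. The text does not say which.

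The effects and correlations are assumed. With strong effects (OR 4) Qc alone is significant in only 7% to 14%, and with none in 4% to 5%.

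**Conclusion.** The point holds. The analysis fixed for the second primary aim tests LVEF and peak Qc each against zero and contains no test between them, so it cannot by itself decide the stated hypothesis. The double use of study group and the entry of GLS beside LVEF add ambiguity and a possible tilt toward Qc. If the result were read from which marker reaches significance, equally good markers would produce the favoured pattern in roughly 12% to 42% of trials for OR of about 1.5 to 3 per SD. A direct contrast errs at close to its nominal level. The contradiction between hypothesis and analysis rests on the text alone; the size rests on the assumed effects, correlations and pooled model. The finding is that the deciding comparison is absent, not that the regression is unusable or that a faulty rule has been adopted.

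**What to change.** Name one direct contrast as the deciding test for this aim and state it in the protocol or analysis plan:

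- Fit one model pooled over arms, with age and study group as covariates.
- Choose one Qc measure (peak Qc, or change from rest) and one visit before the outcome (baseline or 4 months), the same for both markers.
- Use either (a) the difference between the Qc and LVEF coefficients, both standardised and coded so that risk runs in the same direction, preferably without GLS or with GLS only in a sensitivity analysis; or (b) the paired AUC difference between two models sharing age and group, one adding LVEF and the other Qc.
- Declare superiority only if the two-sided 95% confidence interval lies wholly on the side favouring Qc.
- Keep the five-variable model as written, the within-arm fits and the dichotomised cut-offs as supportive.

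The cost is wording. The measurements are already scheduled at every visit, and the trial was still recruiting at submission. The price is a harder claim: at 90 women, with OR of about 3 for Qc and 1 for LVEF, power is about 54% for (a), calculated with GLS in the model, and about 40% for (b). It falls to about a quarter or less if LVEF also predicts at OR 1.5. That should be acknowledged beside the 90.

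### The 90-women figure for the second primary aim counts predictors only; it takes no account of the roughly 22 expected events or of the LVEF-versus-Qc comparison, and the wording on study group is inconsistent

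*Protocol article*

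**What the plan says.** All of this is in the protocol article. In the section on sample size calculation and statistical analysis the overall claim is that "Our sample size of 100 subjects will address Aims 1 and 2", with allowance for 10% attrition. For the exercise comparison, which that section calls Aim 1, the plan assumes 36% disabled under usual care and 12% under exercise training; overall, "we have used a conservative 24% incidence of functional disability".

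For the second primary aim, the target of prediction is "identifying women who will meet criteria for functional disability at 12 months". The outcome section defines this as a threshold: "prevalence of functional disability (defined as VO_2_peak ≤ 18.0 mL/kg/min) measured via CPET at 12 months". The Background gives the hypothesis that cardiac reserve will be superior to resting LVEF as a predictor.

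The analysis is a regression with "five variables entered (age, LVEF, GLS, study group and peak Qc"). The next sentence adds: "The analysis will be stratified for group allocation (usual care vs exercise training"), with the stated purpose of accounting for a possible effect of the intervention on incidence. The sample size for this analysis "can be calculated as 90 women (50 + 8 x no. of variables").

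**The concern.** Two things look wrong.

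- **The sizing rule takes no account of what limits this analysis.** With a yes/no outcome, the information comes mainly from the number of women who become disabled. The formula returns 90 whether 5% or 50% of women have the outcome. It contains no effect size, no power and no difference between LVEF and Qc, although that difference is the hypothesis.
- **Study group is used in two incompatible ways.** If the analysis is run separately by arm, group is constant within each arm and its coefficient cannot be estimated. If group is a covariate, the analysis is pooled and not stratified in that sense.

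At stake is how a primary result is read. With few events, a failure to separate Qc from LVEF says little, and an apparent advantage for Qc may be imprecise. A reader told that the trial was sized for this aim would trust either result more than the data allow.

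**Working it through.** **Inputs from the protocol article:** 100 randomised 1:1; 10% attrition, hence 90 evaluable and 45 per arm; 36% (usual care) and 12% (exercise), which average 24%; 29% in the pilot; five predictors; 5% significance level.

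**1. The plan's figure.** 50 + 8 × 5 = 90, and 90 / (1 − 0.10) = 100. Both reproduce exactly.

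**2. Expected events, one pooled model.**
- Usual care: 45 × 0.36 = 16.2
- Exercise: 45 × 0.12 = 5.4
- Total: 21.6, the same as 90 × 0.24
- Events per variable: 21.6 / 5 = 4.3
- At the pilot's 29%: 90 × 0.29 = 26.1 events, 5.2 per variable

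**3. Precision for a single AUC.** The documents give no AUC, so 0.75 is an assumption. The Hanley-McNeil variance, with n1 women with and n0 women without the event, is

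[A(1 − A) + (n1 − 1)(Q1 − A²) + (n0 − 1)(Q2 − A²)] / (n1 n0), where Q1 = A/(2 − A) and Q2 = 2A²/(1 + A).

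For A = 0.75, Q1 = 0.600 and Q2 = 0.643. With n1 = 21.6 and n0 = 68.4 the standard error is 0.066, and the 95% half-width is 1.96 × 0.066 = 0.13.

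**4. Power for the comparison.** The standard error of the difference is √(SE₁² + SE₂² − 2r SE₁SE₂), where r is the correlation between the two AUC estimates. Power is approximately Φ(difference/SE − 1.96), two-sided 5%. The AUCs and r are all assumptions.

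| Qc vs LVEF (AUC) | r = 0 | r = 0.4 |
|---|---|---|
| 0.75 vs 0.65 | 18% | 26% |
| 0.80 vs 0.65 | 36% | 54% |
| 0.80 vs 0.55 | 75% | 92% |

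At r = 0.6 the first two rows rise to 37% and 71%. The answer depends on assumptions that the plan does not state.

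**5. The two readings of the group wording.**
- *One pooled model with group as covariate.* Five variables and 90 women: the 50 + 8m count is met. Steps 2 to 4 apply.
- *Separate models per arm.* Group drops out, leaving four predictors. The same rule gives 50 + 8 × 4 = 82 per arm (164 in total) against 45 available. Events per variable are 16.2 / 4 = 4.05 in usual care and 5.4 / 4 = 1.35 in the exercise arm. The chance of four or fewer events in the exercise arm, Binomial(45, 0.12), is 36%.

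**The case against.** The best defence is that the plan means one pooled model. Stratification is said to serve to account for the intervention, which is the language of adjustment. Study group is counted among the five variables, and the rule is applied once to the whole sample. Read this way, 90 women satisfy the rule. This stands, so a reader who infers that the plan breaks its own rule, or that it rests on an exercise-arm model with five events, goes further than the documents allow. Those figures hold only under a literal per-arm reading, and separate per-arm models are never explicitly described.

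Nor do the documents show that the comparison is bound to be underpowered. The protocol's premise is that resting LVEF is a weak marker. If LVEF had an AUC of 0.55 and Qc one of 0.80, power would be 75–92% at correlations of 0 to 0.4. Simulation of the pooled five-variable model, with independent predictors, gives 73% power to detect one predictor at an assumed odds ratio of 2 per SD (35% at 1.5, 97% at 3). That, however, concerns the association of one predictor, not superiority over another.

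It is also tempting to say that the cited rule was devised only for continuous outcomes. The source is not at hand, and this point does not rely on it; the formula as printed is enough.

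Finally, the type of regression and the exact test may be set out in an analysis plan that is not shown, and their absence is not the complaint. The defence leaves untouched that the stated justification uses neither events nor the comparison, and that the group wording contradicts itself.

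**Conclusion.** The point holds in a limited form. The 90 is computed correctly, but it does not support the claim that 100 women address the LVEF-versus-Qc comparison. On the plan's own 24% and 10% attrition, about 22 events are expected for five variables (4.3 per variable). An assumed AUC of 0.75 would then be known to about ±0.13. Power for superiority is not stated and runs from 18% to 92% over the AUC pairs tabulated at correlations of 0 to 0.4, so neither adequacy nor inadequacy can be asserted from the document.

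The wording on study group is wrong under either reading. Under the more natural pooled reading, that part is a drafting error only. Under the literal per-arm reading, 45 women per arm fall short of 82, and the exercise arm has about 5 events for four predictors. The randomised comparison of exercise with usual care is not affected.

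**What to change.** In the paragraph on the second primary aim:

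1. Delete the stratification by group allocation and keep study group as a covariate in one pooled logistic model. Penalised (Firth) estimation is preferable with so few events.
2. Replace the 90-women justification with the expected number of events (about 22 among 90 evaluable women) and the precision this gives (95% CI half-width about 0.13 for an assumed AUC of 0.75).
3. State that no power is claimed for superiority of Qc over LVEF. If power is quoted, give it as a range over stated AUCs and correlations, as in the table above.
4. Bring the general statement that 100 women address both aims into line with this.

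The cost is protocol and analysis-plan wording. No extra patients are needed. The downside is that the stated adequacy for this aim becomes less favourable.
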